### 2.7. Data Analysis

The service delivery bundle will be reviewed as a prospective, observational program assessment using a pre–post design.

Quantitative Analysis: Clinical and implementation indicators (Table 2 and Table 3) from the baseline period (3 months prior to implementation) will be compared with the final period (last 3 months of the project). Data will be analyzed using analysis of variance, unpaired and paired t-tests, and chi-square analysis as appropriate.Qualitative Analysis: Qualitative data from staff interviews and debriefs will be transcribed and subjected to thematic analysis to identify operational bottlenecks and assess the acceptability and feasibility of the service delivery bundle.

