## 2. Materials and Methods

### 2.1. Implementation Design and Timeline

The longitudinal review of this protocol will utilize a Hybrid Type 1 effectiveness-implementation design. This approach allows for the primary review of the clinical effectiveness of the maternal and newborn bundle on patient outcomes, while simultaneously observing and gathering data on its feasibility, acceptability, and sustainability within the targeted facilities. The review employs a prospective, quasi-experimental before-and-after design.

Routinely collected service-delivery data from the three months immediately before implementation will be compared with data from the final three months of the 36-month implementation period, with continuous monitoring throughout. This design was selected for three reasons. First, the bundle is delivered as a facility-level package of training, equipment, mentoring, and supervision; patient-level randomization would not preserve intervention integrity. Second, withholding the bundle from comparable facilities is ethically difficult given Sierra Leone’s mortality burden and the established effectiveness of each component. Third, all participating facilities report to the national District Health Information System 2 (DHIS2), providing a long retrospective time-series that strengthens within-facility comparisons. Limitations arising from the absence of concurrent control are discussed in Section 3.5. Implementation will be divided into three phases:Preparatory Phase: Baseline analysis and equipment procurement. Based on these findings, a causal/bottleneck analysis of the adequacy of perinatal care quality will be conducted and shared with hospital administrations, and mitigation plans will be prepared.Implementation Phase (months 1–18): Training of trainers and equipment deployment. Training scale-up, mentoring, and supportive supervision, to include midwives, nurses, surgical and community health officers, and physicians (2024–2025).Sustainability Phase (months 19–36): Continue supportive supervision and transition to MoHS ownership (2026–2027).

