### 2.3. Implementation (The Service Delivery Bundle)

The service delivery bundle comprises a newborn package and a maternal package, supported by cross-cutting implementation strategies.

Newborn Care PackageCurriculum: Implementation of the World Health Organization Essential Newborn Care Course (ENCC) Parts 1 and 2.Respiratory Support: Training and deployment of Vayu bCPAP systems and Vayu oxygen blenders to prevent hyperoxic lung injury and retinopathy of prematurity.Equipment: Provision of bag-and-mask devices, suction units, heart rate monitors, and pulse oximeters, in addition to Vayu bCPAP systems, oxygen blenders, and consumables.Kangaroo Mother Care (KMC): Expansion of KMC, to ensure neonatal euthermia, for the immediate care of small and sick newborns.Maternal Care PackagePPH Management: Implementation of the WHO Postpartum Hemorrhage Package, including blood-loss quantification aids, intrauterine balloons, and anti-shock garments.Advanced Diagnostic Equipment: Training and deployment of Butterfly iQ3 handheld ultrasound probes (POCUS) for delivery wards and point-of-care hemoglobin testing.Risk Stratification: Enhanced triage and risk assessment using handheld ultrasound, improved use of fetal Dopplers and sphygmomanometers, and hemoglobin testing.Cross-cutting StrategiesRespectful Care: Principles and practices of respectful care will be integrated into clinical training and mentoring activities.Infection Control and Prevention (IPC) Supplies: Refresher training and supplies to improve water, sanitation, and hygiene practices.Service Optimization: Facility-based teams will identify unique challenges and implement and document improved practices.Implementation StrategyMentorship: Project HOPE will supply external mentors to cascade training and provide supportive supervision while observing patient care practices.Champions: Two internal “Champions” will be recruited at each facility to support training scale-up and practice.Practice Corners: Establishment of LDHF practice stations for skills retention.Ancillary Services, Equipment, and SuppliesData: Mentoring healthcare staff with documentation challenges and collecting and cleaning data.Equipment: Ancillary equipment includes Dopplers, stethoscopes, pulse oximeters, sphygmomanometers, thermometers, glucometers, oxygen concentrators, heart rate monitors, resuscitation equipment, and training simulators.Supplies: Consumables for bCPAP, hemoglobin, and urine testing, WASH equipment and supplies, personal protective equipment and sanitation supplies, hemorrhage kits and commodities, and printed materials.

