#### 2.4.2. Implementation Outcomes

Implementation success will be evaluated through metrics of fidelity, uptake, and sustainability:Fidelity and Adherence: The proportion of eligible SCBU admissions successfully initiated on Vayu bCPAP; the proportion of deliveries utilizing active management of the third stage of labor (AMTSL) with uterotonics; and the proportion of obstetric admissions receiving triage ultrasound scans.Uptake and Penetration: The total number of healthcare workers (midwives, nurses, physicians) successfully completing the WHO ENCC and PPH training modules against facility targets.Sustainability and Retention: The frequency of documented low-dose high-frequency (LDHF) practice sessions per facility; and objective skills retention measured via Objective Structured Clinical Examinations (OSCEs) at 12-month intervals.

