**Figure 2 mps-09-00096-f002:**
[figure not shown]
Implementation logic model.

**Table 1 mps-09-00096-t001:** Baseline characteristics and target training populations of participating healthcare facilities (2023).

Facility Name	Location (City)	Number of Annual Births	Maternal Deaths (2023)	Neonatal Deaths (2023)	Number of Annual C/S	Healthcare Workers Trained in Past 2 Years	Total Healthcare Workers to Be Trained
Bo Government Hospital	Bo	3226	34	191	1053	28	23
Jenner Wright Clinic	Freetown	412	17	6	14	13	-
King Harman Road Government Hospital	Freetown	712	8	15	331	9	87
Kissy CHC	Freetown	440	17	4	3	19	-
Princess Christian Maternity Hospital	Freetown	7099	63	464	3016	12	125
Rokupa Government Hospital	Freetown	1495	1	54	599	5	65
Ross Road CHC	Freetown	626	3	1	3	29	-
St. Anthony’s CHC	Freetown	511	19	2	5	27	-
Waterloo CHC	Waterloo	1015	17	11	20	8	23

**Table 2 mps-09-00096-t002:** Education and training.

Category	Indicator	Definition
Training uptake	Number of healthcare workers trained	Total number of midwives, nurses, physicians, and other staff completing WHO ENCC and PPH training modules
	Training completion against targets	Number completing training/facility training target
Skills retention	Frequency of LDHF practice sessions	Number of documented low-dose, high-frequency practice sessions per facility
	OSCE performance scores	Percentage of participants achieving competency on Objective Structured Clinical Examinations (OSCEs)
	Skills retention at 12 months	Percentage of trained staff maintaining competency at 12-month reassessment
Mentorship and supervision	Mentorship visits completed	Number of supportive supervision and mentorship visits conducted per facility
	Practice corner utilization	Frequency of use of facility-based LDHF practice stations

**Table 3 mps-09-00096-t003:** Maternal and newborn measures with definitions.

Category	Indicator	Definition
Maternal indicators	PPH incidence (500 cc)	[# of PPH incidence (500 cc)]/[total births]
	Uterotonics used for PPH prevention	[# of uterotonics used for PPH prevention]/[total births]
	Direct obstetric case fatalities	[# maternal deaths]/[# of total births]
	Admission triage scans	[# of ultrasound scans]/[# of maternal admissions]
	Abnormal scan findings	[# of abnormal scans]/[# of scans]
Neonatal indicators	Fresh stillbirths	[# of fresh stillbirths]/[total births]
	Neonatal case fatality rate < 24 h	[# of neonatal deaths < 24 h]/[total births]

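### Section 2.7 applies one before-versus-final comparison to every indicator, but the Table 2 education indicators have no usable baseline and section 2.4.2 defines them on a different time frame

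*Protocol article*

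**What the plan says.** The protocol article's section 2.7 (Data Analysis) sets one rule for both indicator tables: "Clinical and implementation indicators (Table 2 and Table 3) from the baseline period (3 months prior to implementation) will be compared with the final period". Section 2.1 fixes the second window as "data from the final three months of the 36-month implementation period", i.e. months 34–36.

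Section 2.1 also gives the calendar of activities. Training and its scale-up belong to the "Implementation Phase (months 1–18): Training of trainers and equipment deployment" stage. What follows is the "Sustainability Phase (months 19–36): Continue supportive supervision and transition to MoHS ownership" stage, which lists no training scale-up.

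Table 2 (Education and training) holds seven indicators. Training uptake is defined as "Total number of midwives, nurses, physicians, and other staff completing WHO ENCC and PPH training modules", with a companion ratio to the facility target. Retention is "Percentage of trained staff maintaining competency at 12-month reassessment". The others are LDHF session frequency, OSCE competency, mentorship visits and practice-corner use.

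Section 2.4.2 describes the same outcomes without the two windows: a total of completed trainings set against facility targets, LDHF frequency per facility, and "objective skills retention measured via Objective Structured Clinical Examinations (OSCEs) at 12-month intervals". Section 2.3 makes clear that the practice corners and external mentors come from the project ("Establishment of LDHF practice stations for skills retention"). Section 2.6 takes the training and LDHF data from project registers and has the mentorship teams collect the OSCE results.

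**The concern.** A before-and-after comparison needs the indicator to exist in both windows. The Table 2 indicators measure the delivery of the bundle, and before the bundle there is nothing to measure. Comparing them with the quarter before implementation sets a quantity that is zero by design against whatever the project does later.

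The second window causes a separate difficulty. It sits at the end of the sustainability phase, well after the training it is meant to describe, and a retention measure tied to 12 months after training need not fall inside it.

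The Hybrid Type 1 design relies on reading fidelity, uptake and retention alongside the clinical results. If section 2.7 is followed as written, part of that reading is uninformative. The useful question is whether practice and mentoring hold up after handover to the Ministry. A facility whose LDHF sessions fell away sharply after month 18, but did not stop, would still be recorded as improved against zero.

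**Working it through.** The article gives no sample size or event figure for these indicators, so there is no stated number to reproduce. The check is a calendar count plus a comparison of definitions.

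**Inputs**
- Baseline window: the 3 months before implementation (sections 2.1 and 2.7).
- Training months: t = 1 to 18 (section 2.1).
- Final window: months 34–36 (section 2.1).
- OSCE interval: 12 months (section 2.4.2). Whether the clock starts with the trainee or the project is not stated.

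**Step 1: the baseline window, indicator by indicator**
- *Workers trained; completion against target:* these count the project's ENCC and PPH modules from project registers. Section 1.2 says that ENCC, Part 2 in particular, had not been introduced and that the PPH package was not yet in use as an integrated bundle. Baseline: zero by construction.
- *LDHF sessions; practice-corner use; mentorship visits:* set up or supplied by the project. Baseline: zero by construction.
- *12-month retention:* its denominator is trained staff reassessed a year later. Baseline: empty denominator, undefined.
- *OSCE competency:* undefined unless an OSCE is done before training. None is stated or excluded.

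That is 7 of 7 without a pre-training OSCE, or 7 − 1 = 6 of 7 with one in the baseline window. The three Table 3 process indicators that match the fidelity outcomes of section 2.4.2 (uterotonic use, triage scans, bCPAP) have denominators before the project and can be compared. Counting them in, the share without a usable baseline is 7 of 7 + 3 = 10.

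Table 1 does not fill the gap. Its column of workers trained in the past 2 years sums to 28 + 13 + 9 + 19 + 12 + 5 + 29 + 27 + 8 = 150, but it covers two years and names no course.

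**Step 2: the final window**
- Training months inside months 34–36: 0 of 18. Months 19–33, 15 full months, lie between the end of training and the opening of the window.
- 12-month reassessment month = t + 12. For t = 1 to 18 this gives months 13–30, so 0 of 18 monthly cohorts fall in the window. Training in months 34 − 12 = 22 to 36 − 12 = 24 would be needed.
- 24-month reassessment month = t + 24, giving months 25–42. Only t = 10, 11, 12 fall in the window: 3/18 = 16.7% of cohorts if training is spread evenly. Cohorts with t = 13 to 18 would be due in months 37–42, after the project ends.
- If OSCEs instead ran in project-calendar waves at months 12, 24 and 36, the month-36 wave would fall in the window.
- LDHF sessions, practice-corner use and mentorship visits can produce data in months 34–36. Their only defect is the baseline.

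**Step 3: the two sections side by side**

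Section 2.4.2 calls for a cumulative total against a target and for a series at 12-month intervals. A three-month count yields neither, so an analyst cannot follow sections 2.4.2 and 2.7 together for these indicators.

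**The case against.** The strongest reply is that the outcomes are defined well enough elsewhere. Section 2.4.2 sets out what is to be reported, section 2.6 says where the data come from, and section 2.1 promises monitoring throughout. On this view section 2.7 is only loosely worded, and a condensed article may leave time points per indicator to an analysis plan. Much of this stands, and it limits the point in four ways.

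- A reader might infer that these outcomes cannot be derived at all. The documents do not support that: they can be reported as section 2.4.2 defines them.
- A reader might infer that training uptake would compare roughly nothing with nothing. That holds only if uptake is read as a three-month count. Table 2 speaks of a total, and a running total at month 36 would not be near zero.
- A reader might infer that retention would have no observations. That needs a clock starting with each trainee and no training after month 18. The Table 2 definition reads most naturally as a per-trainee clock, but the clock start is not fixed, a wave at month 36 is possible, and the train-the-trainer model leaves room for later sessions.
- A reader might extend the point to the whole implementation side. Uterotonic coverage, triage scans and bCPAP can be compared in both windows. The share of abnormal scans is undefined at baseline only where no scanning took place, which the article does not report.

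What does not stand is that this is merely omitted detail. Section 2.7 states a rule, names both tables and makes no exception; its closing latitude concerns the choice of test, not the windows. Sections 2.5 and 2.6 cite Tables 2 and 3 the wrong way round, but that does not matter here because section 2.7 names both.

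**Conclusion.** The point holds in limited form. For the seven Table 2 indicators, the comparison in section 2.7 has a structural-zero or undefined baseline (six of seven if a pre-training OSCE falls in the baseline window). For LDHF sessions, practice-corner use and mentorship visits, any final-window activity counts as an increase, so the contrast cannot show decline. For training uptake, a three-month count misses the months in which training takes place. For 12-month retention, 0 of 18 monthly cohorts are reassessed in months 34–36, assuming a per-trainee clock and training confined to months 1–18. The rule also conflicts with section 2.4.2.

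No primary clinical outcome is affected, and the data needed for a sensible report are largely planned. This should be corrected because the present wording would give an uninformative implementation result when a useful one is available.

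**What to change.** Reword section 2.7 in two parts.

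1. Limit the baseline-versus-final comparison to indicators measurable in both windows: the clinical indicators, and uterotonic coverage, triage scans and bCPAP. State where a baseline is zero because the service did not yet exist.
2. Analyse the Table 2 indicators as section 2.4.2 defines them:
   - training uptake as cumulative completion against the facility target;
   - OSCE competency at the end of training against the 12-month reassessment, timed from each trainee's training date and paired where trainee-linked scores exist, with 24-month results only for cohorts trained by month 12 (12 + 24 = 36);
   - LDHF sessions, practice-corner use and mentorship visits as rates per facility-month over months 1–18 and months 19–36, reported descriptively. With nine facilities each phase offers 9 × 18 = 162 facility-months.

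If OSCEs are meant to run in project-calendar waves, or a pre-training OSCE is planned, the section should say so.

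Training logs, OSCE results and project registers are already to be collected under section 2.6. The cost is a small amount of extra tabulation and the need to link OSCE scores by trainee, which the article does not describe.

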### 2.8. Ethical Considerations

Because this protocol is structured as a service delivery program review rather than a clinical trial, it does not involve human subjects research. All clinical elements of the newborn and maternal packages are standard, evidence-based practices with ample prior evidence of benefits and minimal risk of harm. The assessment relies exclusively on the secondary analysis of routine programmatic data and information mandated by the Ministry of Health and Sanitation (MoHS). All extracted clinical data will be fully anonymized and aggregated at the facility level, ensuring the de-identification of patient outcomes. Prior to implementation, the project was carefully evaluated by the MoHS and approved.

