### 1.4. Objectives

The primary objective of implementing a targeted service delivery bundle is to enhance maternal and newborn outcomes in a cohort of nine hospitals over a three-year period. These service delivery improvements aim to achieve the following:Reduce neonatal mortality: Achieve a 50% reduction in neonatal deaths within the first 24 h and a 10% reduction in intrapartum or “fresh” stillbirths compared to a baseline assessment.Reduce neonatal morbidity: Achieve a 25% reduction in neonatal transfers to advanced care.Improve neonatal clinical practice: Ensure that 80% of SCBU admissions with respiratory distress receive appropriate oxygen therapy.Reduce maternal morbidity: Achieve a 40% reduction in the incidence of postpartum hemorrhage and a 50% reduction in institutional maternal mortality.Improve obstetric clinical practice: Ensure that 90% of deliveries utilize active management of the third stage of labor with uterotonics to prevent hemorrhage.Strengthening diagnostic capacity: Deploy handheld ultrasound and point-of-care hemoglobin testing to improve obstetric risk stratification.Maintain competency: Implement a “train-the-trainer” model, mentoring, low-dose high-frequency practice, and supportive supervision to maintain high performance on knowledge and skills checks at 12-month intervals.

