#### 2.4.1. Clinical Effectiveness Outcomes

The primary clinical outcomes focus on immediate survival and severe morbidity:Primary Neonatal: Reduction in the neonatal mortality rate within the first 24 h.Primary Maternal: Reduction in the incidence of postpartum hemorrhage (≥500 mL).Secondary Outcomes: Fresh stillbirth rate, institutional maternal case fatality rate, neonatal transfer rate for advanced care, and survival rate of sick newborns admitted to the SCBU.

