### 2.6. Data Collection

Data collection is stratified by outcome type:Clinical Data (See Table 2): Quantitative will be collected from existing Ministry of Health (DHIS2) systems and project-specific sources. Project data collectors will collaborate with medical record officers to extract granular clinical data from consecutive maternity and newborn registers across all nine facilities. A preliminary review for validation and missing entries will be followed by cross-verification. Outcomes observed during the implementation and sustainability periods will be compared with retrospective baseline data collected three months prior to training.Implementation and Educational Data (See Table 3): Quantitative implementation metrics, including training logs and low-dose high-frequency (LDHF) practice frequencies, will be extracted from facility-level project registers. Educational indicators, such as performance on objective structured clinical examinations (OSCEs) and skills retention at 12 months, will be collected and tabulated by the mentorship teams.Qualitative data: Qualitative insights regarding implementation barriers and skill retention will be obtained from selected facility staff interviews, debriefs, and surveys.

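### The primary 24-hour newborn death rate is a crude comparison from facility-level aggregates, so a change in the birthweight mix of births could not be separated from a change in survival

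*Protocol article*

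**What the plan says.** Five statements in the protocol article bear on this point.

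- **Extraction (2.6).** Data collectors will "extract granular clinical data from consecutive maternity and newborn registers across all nine facilities".
- **Aggregation (2.8).** "All extracted clinical data will be fully anonymized and aggregated at the facility level, ensuring the de-identification of patient outcomes".
- **Outcome (2.4.1, 1.4).** The primary newborn outcome is "Reduction in the neonatal mortality rate within the first 24 h", and the stated aim is to "Achieve a 50% reduction in neonatal deaths within the first 24 h".
- **Indicator (Table 3).** The numerator and denominator are given as "of neonatal deaths < 24 h]/[total births". No birthweight or gestational-age stratum is attached, and birthweight is not named as a variable anywhere in the article.
- **Comparison (2.1, 2.7).** "Routinely collected service-delivery data from the three months immediately before implementation will be compared with data from the final three months" of the 36-month programme. The methods are: "Data will be analyzed using analysis of variance, unpaired and paired t-tests, and chi-square analysis as appropriate".

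Section 3.5 acknowledges the lack of a control group and lists other programmes, hospital maintenance and external factors as possible influences. It does not mention a change in the kind of births that the facilities receive.

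**The concern.** A crude before-after rate mixes two things: the risk of death for a baby of a given size, and the sizes of the babies born in the facilities. If first-day mortality is much higher in very small babies, a change in their share of births moves the crude rate even when care is unchanged. It moves it upward or downward, depending on the direction of the change.

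Nothing in the described comparison separates the two. The windows start 36 months apart, there is no concurrent control, the named tests are unadjusted, and the one stated aggregation rule mentions no stratum. If birthweight is not carried through the aggregation step, nobody can later check from that file whether a fall in the primary outcome reflects better survival or a different mix of births.

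**Working it through.** The article states no baseline 24-hour rate, event count, sample size or power, so there is no figure of its own to reproduce. The question is how large the distortion could be.

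**Inputs from Table 1 (2023).** The nine facilities sum to 15,536 births and 748 neonatal deaths, which is 748/15,536 = 48.1 per 1000, age at death not given. A three-month window holds about 15,536/4 = 3,884 births.

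**Assumed inputs (not in the article).**
- Baseline 24-hour rate p: 12, 16, 24 or 36 per 1000, that is 25%, 33%, 50% or 75% of 48.1.
- Share of very small babies s: 1%, 2% or 3%.
- Their 24-hour mortality m1: 20%, 30% or 50%.

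**Formulas.** The crude rate is p = s·m1 + (1 − s)·m0, so m0 = (p − s·m1)/(1 − s). With care unchanged, a change d in the share moves the crude rate by d·(m1 − m0). The targeted 50% reduction is p/2. The ratio of the two is the distortion as a fraction of the target.

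Central case: m0 = (0.016 − 0.02 × 0.30)/0.98 = 0.0102. A half-point change gives 0.005 × (0.30 − 0.0102) = 1.45 per 1000, against a target of 8 per 1000, or 18%.

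| Case | p per 1000 | s | m1 | m0 per 1000 | Shift per 1000, d = 0.5 point | Fraction of target | Shift per 1000, d = 1 point | Fraction of target |
|---|---|---|---|---|---|---|---|---|
| Smallest | 36 | 1% | 20% | 34.3 | 0.83 | 5% | 1.66 | 9% |
| Central | 16 | 2% | 30% | 10.2 | 1.45 | 18% | 2.90 | 36% |
| Largest | 12 | 2% | 50% | 2.0 | 2.49 | 41% | 4.98 | 83% |

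Of the 36 combinations, one is impossible (3% × 50% = 15 per 1000, above a baseline of 12). Of the other 35, a half-point change never reaches half the target. A one-point change exceeds half in five, all with 50% mortality and a baseline of 12 or 16 per 1000. In the central case, mimicking half the target takes a change of 4/289.8 = 1.4 points.

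**If the bundle truly halves risk in both groups.** The observed rate is 0.5·(p ± shift). In the central case a one-point rise gives 0.5 × 18.9 = 9.45 per 1000, an apparent fall of 1 − 9.45/16 = 41%. A one-point drop gives 0.5 × 13.1 = 6.55, an apparent fall of 59%. In the largest case a one-point rise gives 0.5 × 16.98 = 8.49, an apparent fall of 29%.

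**Scale of the share change.** Chance alone moves a 2% share between two windows by about ±1.96·√(2 × 0.02 × 0.98/3,884) = ±0.6 points. That chance part already sits in the sampling error of the crude rates, so it is not extra bias. A systematic change of the same size would be.

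**Contrast with facility mix.** The tertiary hospital has 464/7,099 = 65.4 neonatal deaths per 1000 and the other eight sites 284/8,437 = 33.7. A five-point change in its share of births moves the all-neonatal-death rate by 0.05 × 31.7 = 1.6 per 1000, about 7% of a 50% reduction (24.1). Facility totals would allow a correction for this. They would not allow one for birthweight.

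**The case against.** **This is a condensed article, and adjustment may sit in an analysis plan that is not shown.** This stands in part: the absence of named covariates is not a finding. The point rests on what the article does fix, a crude indicator and an aggregation rule. A later plan can standardize only if the strata survive aggregation.

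**Section 2.8 is a de-identification statement, not a file specification.** This stands. A reader might infer that 2.6 and 2.8 contradict each other, or that correction becomes impossible. Neither follows. Detailed extraction followed by aggregation is a coherent sequence, facility-level aggregation does not strictly exclude counts by birthweight band, and the registers might allow re-abstraction. The supportable statement is that the file as described does not provide for the separation.

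**No shift in mix is shown.** This also stands. Table 3 measures ultrasound as admission scans, babies transferred in after birth do not enter a denominator of births, and movement among the nine sites cancels in a pooled rate. It would not cancel in paired facility comparisons, however, and section 2.1 counts within-facility comparison as a strength. Births moving into or out of the network would affect the pooled rate too. Section 1.1 itself expects ultrasound to prompt earlier referral.

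**The size has no anchor in the article.** This is correct. A reader might infer that a small change in the share of very small babies could create or erase much of the 50% effect. The figures do not support that as a general statement. At a baseline of 36 per 1000 even a one-point change is 9–27% of the target, and starting from a 2% share, one point is half as many very small babies again.

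**Section 3.5 already mentions external factors.** Only partly an answer: it does not tell the reader that the mix of births may differ between the windows.

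**Conclusion.** The concern holds in a limited form. The indicator, the aggregation rule and the unadjusted, uncontrolled comparison together leave a change in birthweight mix confounded with the bundle's effect on the primary newborn outcome, and the limitations section does not say so.

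The likely size is material rather than dominant: about a fifth of the targeted reduction for a half-point change and about a third for a one-point change in the central case, with wide ranges. This rests wholly on assumed baseline rate, share and mortality, and on the mix actually changing, for which the article gives no evidence either way. It is a cheap improvement worth making before the data are aggregated, not a flaw that invalidates the comparison.

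**What to change.** If the registers record birthweight, which the article does not say:

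1. **Section 2.8:** state that data are anonymized and aggregated by facility, period and birthweight band (for example <1500 g, 1500–2499 g, ≥2500 g and *not recorded*), abstracted identically in both windows, with small cells suppressed in publication. This keeps the de-identification aim.
2. **Section 2.7:** report the 24-hour death rate by band. Beside the crude ratio, give a ratio standardized to the baseline birthweight distribution: Σ(baseline share × final-period rate) / Σ(baseline share × baseline rate), summed over bands. Show it with and without the *not recorded* band.
3. **Section 3.5:** name a change in case mix between the windows as a limitation. This applies even if birthweight proves unavailable.

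The cost is one extra abstraction field, one extra table and a few sentences. The downsides are missing or rounded birthweights in the retrospective baseline, and sparse cells at the community health centers, so the standardized ratio is best computed on pooled data. The crude indicator stays as defined.
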